### Statistical analysis

Baseline characteristics will be summarised by treatment group to assess comparability. We are not planning to adjust the analyses for baseline variables.

Data analysis will be performed according to the intention-to-treat principle. The primary outcome will be analysed by a comparison of scores using an independent t test, with 95% confidence intervals and two-tailed p values reported. Significance levels will be set at 0.05.

The 24-h opiate usage and hospital length of stay will by analyses using independent t tests with 95% confidence intervals and two-tailed p values reported.

Nausea and vomiting will be recorded as categorical variables and analysed using the Pearson chi-squared test.

For the analysis of pain scores across the four periods a linear regression analysis will be used with the dependent variable being the pain score and the independent variables being ‘period’, ‘group’ and ‘period*group’ interaction. This analysis will be conducted within the framework of Generalised Estimating Equations, which corrects the bias in the estimates of the SE caused by having multiple observations per person and thus correlation in the data. The output generated would be the difference between the groups across all periods (95% CI and p value) and the difference between the groups in each period (95% CI and p value).

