## Methods

### Design

This is a protocol for a pragmatic, multi-centre, blinded, parallel-group, randomised controlled placebo trial. The trial is being conducted in two metropolitan academic hospitals in Sydney, Australia (Macquarie University Hospital and Nepean Public Hospital).

All patients will undergo general anaesthesia (GA). The patients randomised to the intervention group will have a SCPB administered under ultrasound guidance with a local anaesthetic solution, whilst patients randomised to the placebo group will be injected with a saline solution. All patients will be admitted to the high dependency unit (HDU) post-operatively, which is routine practice in the primary centre.

The primary endpoint is the QoR-40 score at 24 h after surgery. It will be measured by blinded assessors. A participant timeline can be found in Fig. 1.

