### Study population and recruitment

Consecutive patients who present to one of the trial neurosurgeons rooms, hospital clinic or hospital emergency department will be assessed for eligibility after they have been consented to undergo ACSS. There are no financial incentives to patients or investigators to encourage enrolment. The eligibility criteria are listed below.

Inclusion criteria:
Age ≥ 16 years oldUndergoing anterior cervical discectomy and fusionUndergoing anterior cervical disc arthroplastyIsolated cervical spine trauma requiring anterior fusion only

Exclusion criteria:
Multi-traumaUndergoing anterior cervical vertebrectomy and reconstructionUndergoing posterior fixation in addition to anterior surgeryUndergoing surgery for malignancyAllergy to ropivacaine or bupivacainePregnant patientsNeurologic or psychiatric condition that would prevent completion of the QoR-40 questionnaire

If the patient meets the eligibility criteria, they will be provided with a patient information and consent form, and be given time to read it, before undergoing an informed consent process with their treating neurosurgeon. All patients will receive a study enrolment number and baseline data will be obtained. Patients will be free to withdraw from the study at any time without giving a reason.

In addition to standard demographic information, other baseline data collected will include smoking history, pre-operative opioid use, adjuvant analgesia use, indication for ACSS and history of previous spine surgery.

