### Randomisation

A patient will be randomised to the study once they have met the eligibility criteria. The randomisation of participants will occur via a central computer generated randomisation service—the Macquarie Clinical Trials Unit (who will not be involved in patient care, data collection or analysis). The day prior to surgery, the pharmacy will receive the randomisation code via email, allocating the patient to one of the two groups.

Due to expected differences in dissection technique, stratified randomisation will be performed based on the number of levels operated on (dichotomised to ≤2 or >2).

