### Sample size calculation

The primary endpoint is the QoR-40 score at 24 h post-operatively, and thus, we are planning a study of a continuous response variable from independent control and experimental subjects with 1 control per group. We used an MCID of 7.5 for the QoR-40, as discussed above. If the true difference between the groups is 7.5, we will need a study of 64 subjects in each group to be able to reject the null hypothesis that the population means of the experimental and control groups are equal with probability (power) 0.8. The type 1 error associated with this test of the null hypothesis is 0.05.

Allowing for a dropout rate of 5%, we will randomise 136 patients (68 in each group). The software used to do the calculation was PS from the University of Vanderbilt, USA.

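### The primary t test ignores the number-of-levels stratum used in randomisation, so it is mildly conservative and forgoes a little power if the stratum is prognostic

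*Protocol article*

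**What the plan says.** All references are to the protocol article.

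- **Randomisation:** "stratified randomisation will be performed based on the number of levels operated on", split at ≤2 versus >2. The reason given is that the surgical dissection is expected to differ.
- **Statistical analysis:** "We are not planning to adjust the analyses for baseline variables". The primary outcome is compared by an independent t test, "with 95% confidence intervals and two-tailed p values reported". Opioid use and length of stay also get t tests. The pain model contains only period, group and their interaction.
- **Sample size calculation:** "If the true difference between the groups is 7.5", 64 evaluable patients per group allow the null hypothesis that the means "are equal with probability (power) 0.8" to be rejected. "The type 1 error associated with this test of the null hypothesis is 0.05". A 5% dropout allowance raises this to 68 per group, 136 in all.
- **Design:** "The trial is being conducted in two metropolitan academic hospitals in Sydney, Australia". Site is not named as a stratification factor.
- **Study population and recruitment:** baseline data include "smoking history, pre-operative opioid use, adjuvant analgesia use, indication for ACSS and history of previous spine surgery".

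**The concern.** A factor important enough to stratify on is left out of the analysis, and no reason is given. Stratified allocation makes the two arms nearly equal in their mix of ≤2-level and >2-level patients, so the estimated treatment difference varies less over repeated trials than under simple randomisation. The t test does not know this: it builds its standard error from the total within-arm variance, including the part that lies between strata. When the stratum is prognostic, the reported standard error exceeds the true sampling variation.

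At stake is precision. The Discussion section acknowledges that 80% power might be thought low and that a type II error is possible, and the Abstract says that a null result would count as evidence that the block is unnecessary. An interval wider than the design warrants weakens that reading somewhat.

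**Working it through.** **1. Reproduce the plan's figure.** Inputs: difference 7.5, two-sided alpha 0.05 and power 0.80 (Sample size calculation and Statistical analysis), and SD 15 (Primary outcome; not repeated in the sample size section). The normal approximation gives 63 per group. The noncentral t gives power 0.7952 at 63 and 0.8015 at 64, so 64 is right. 64/0.95 = 67.4, rounded up to 68 per group, 136 in total. The plan's figure reproduces, and it matches an unadjusted test.

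**2. Variance explained by the stratum.** With share p of patients having >2 levels, a QoR-40 shift of d points and total SD 15:

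R² = p(1 − p)d²/225

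The documents give neither p nor d, so both are assumed:

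- p = 0.20, d = 7.5: 0.16 × 56.25/225 = 0.04
- p = 0.20, d = 10: 0.16 × 100/225 = 0.071
- p = 0.20, d = 15: 0.16 × 225/225 = 0.16
- p = 0.30, d = 15: 0.21 × 225/225 = 0.21

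**3. Standard errors at 64 per group.** The t test reports about 15 × √(2/64) = 2.652 in every case. Under stratified allocation the true sampling SD is about 2.652 × √(1 − R²). For R² = 0.04 that is 2.60, for 0.071 it is 2.56, for 0.16 it is 2.43 and for 0.21 it is 2.36.

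**4. Simulation.** 128 patients, permuted blocks of 4 within stratum (an assumed block size), total SD 15, true difference 0 or 7.5. There were 15,000 runs per setting, and 20,000 for the 10-point row. "Adjusted" means a linear model with group and stratum.

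| Share >2 levels | Shift | t-test mean SE | True SD | t-test type I error | Power, t test | Power, adjusted |
|---|---|---|---|---|---|---|
| 20% | 0 | 2.65 | 2.65–2.66 | 5.1% | 80.4% | 80.5% |
| 20% | 7.5 | 2.65 | 2.58 | 4.3% | 80.5% | 81.7% |
| 20% | 10 | 2.65 | 2.54–2.57 | 4.2% | 80.9% | 82.8% |
| 20% | 15 | 2.65 | 2.44 | 3.1% | 82.6% | 86.7% |
| 30% | 15 | 2.65 | 2.36–2.37 | 2.9% | 83.0% | 88.7% |

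The simulated standard errors agree with step 3. The adjusted test's type I error stayed between 4.8% and 5.1%.

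**5. Further covariates, for precision only.** With residual SD 15√(1 − R²), 64 per group and 125 degrees of freedom, an assumed total R² of 0.05, 0.10 or 0.20 gives power of 82.1%, 84.1% or 88.1%. The last two are equivalent to 64/0.90 = 71 and 64/0.80 = 80 patients per group analysed without adjustment.

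**The case against.** The best defence is that nothing here is invalid. The estimate is unbiased, type I error is at or below 5%, and the sample size was computed for the test that will be used. A pre-specified unadjusted comparison is simple and leaves no room for choosing covariates after the fact. All of that stands, and it limits the point to efficiency. It does not justify leaving out the stratum, which can be pre-specified just as firmly and costs essentially nothing when it has no effect (first row of the table). Nor is this a detail left to an unseen analysis plan: the protocol rules adjustment out, so a plan that adjusted would contradict it.

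Four stronger readings are tempting but not supported:

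- *Omitting site and pre-operative opioid use also makes the standard error too large.* That holds only for a factor balanced by design, and the Randomisation section names only the number of levels. For the others the unadjusted standard error is valid, and the sole cost is precision not gained.
- *The trial falls short of its planned power.* In every setting simulated, the t test kept at least about 80%. The loss is relative to the adjusted analysis.
- *Adjustment would bring power to 88%.* This needs a total R² of about 20%, which the documents do not give.
- *The protocol expects QoR-40 to differ by number of levels.* It says only that dissection technique is expected to differ. An effect on QoR-40 is plausible but not stated.

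**Conclusion.** The mismatch between stratified randomisation and an analysis that excludes the stratum is explicit, and the direction of its consequence is certain whenever the stratum is prognostic: a standard error that is too large, an interval that is too wide and a mildly conservative test. The size is uncertain because it depends on an assumed share and shift. The range runs from nothing (no stratum effect), through about 1 to 2 power points (20% share, 7.5- to 10-point shift), to about 4 (20%, 15 points) or 6 (30%, 15 points). A 15-point shift equals a full SD and twice the difference the trial is designed to detect, so the lower part of the range is the more cautious expectation. The point concerns efficiency, not validity, and the planned 136 patients need not change.

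**What to change.** Replace the no-adjustment sentence. Make the primary analysis a linear model of 24-h QoR-40 on treatment and levels stratum (≤2/>2), reporting the adjusted mean difference with its 95% confidence interval and two-sided p value. Keep the independent t test as a sensitivity analysis. Add the stratum term to the analyses of opioid use and length of stay and to the pain-score model.

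Optionally, pre-specify site and pre-operative opioid use as further covariates, stating that they are there for precision only.

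The cost is a short amendment to the analysis text, submitted to the two ethics committees and updated on the registry as the protocol requires for any modification. The stratum is known at randomisation, and site and opioid use are already recorded, so no new data are needed. The change should be made while the data are still blinded; the Trial status section reports 17 patients recruited so far.

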### Data collection and storage

All forms will be completed in English. Data will be collected directly from patients after enrolment. All paper copies of collected data will be stored in a locked filing cabinet in the Chief Investigator’s office and will be identified by the patient’s study enrolment number. The database of patient’s names and enrolment numbers will be stored on a password protected hard drive, thus preserving the de-identification of the paper copies.

All data will be entered in to an electronic trial database stored on a password protected external hard drive that will remain in the office of the chief investigator. The QoR-40 questionnaire will be completed by the patient with an investigator 24 h after surgery. Patients will follow-up with their treating neurosurgeon 6 weeks after surgery, and final data collection will occur at this time.

The data analysis will be carried out by the associate investigators in the trial, using the de-identified patient data.

Information and data will be stored for 10 years and then be erased. The Chief Investigators only will have access to the filing cabinet and hard drive.

Deidentified individual participant data that underlies the results reported in this trial will be made available to researchers who provide a written request to the chief investigators within 10 years after the publication of the trial. The request must be methodologically sound, and the researchers will need to sign a data access agreement.

### Ethics and dissemination

Ethics approval has been obtained from the Macquarie University Human Research Ethics Committee (HREC) for the trial to commence at Macquarie University Hospital (Reference No:5201949827706) and from the Nepean Blue Mountains Local Health District HREC to commence at Nepean Public Hospital (Reference 2019/ETH10684).

Any modifications to the protocol will be submitted to the above aforementioned HRECs before implementation, and the protocol will be amended on the ANZCTR website.

All results arising from this trial will be presented at scientific meetings and published in peer-reviewed journals. In addition to publishing the protocol in a peer-reviewed journal, the draft protocol is available for public access on the Australian New Zealand Clinical Trials Registry website. There is no intention to use professional writers.

### Monitoring and safety

All adverse events will be recorded. When a serious adverse event occurs, it will be reported immediately to the Macquarie University HREC or the Nepean Blue Mountains Local Health District HREC. The chief investigator will review all documentation related to the event and provide a written report to the HREC. Annual reports to the HREC are planned. There will not be an interim analysis or data monitoring committee: this trial is anticipated to be of a relatively short duration, is evaluating low risk interventions, is not evaluating a new treatment and is not influenced by industry.

Adverse events related to the SCPB to be recorded are as follows:
Allergic reaction to local anaesthetic solutionLocal anaesthetic toxicityAccidental intravascular injection of local anaestheticSCPB site haematomaUpper limb paresisHorner’s syndromePhrenic nerve palsy

Each adverse event has a less than 1% chance of occurring with this procedure. If life-threatening adverse event occurs in the intra-operative period, unblinding will occur when the anaesthetist for the case calls pharmacy to request emergency unblinding.

## Discussion

Here, we present the protocol for a randomised controlled trial evaluating the role of SCPB in ACSS. The trial is unique as it is the first placebo trial and the first completely blinded trial of its nature. This protocol conforms to the Standard Protocol Items: Recommendations for Interventional Trials [22].

Whilst SCPB has been studied in thyroid and carotid surgery, there is a paucity of evidence for performing SCPB for ACSS. A single centre, non-blinded, randomised controlled trial (RCT) comparing GA to awake surgery with bilateral deep and superficial cervical plexus blocks found a trend towards better post-operative pain control in the cervical plexus block group. The GA group however had better intra-operative haemodynamic stability and patient satisfaction scores [23]. It has been shown that SCPB is preferred to deep cervical plexus block, as the deep block is associated with a greater risk profile without conferring a significant benefit [10].

The only trial we are aware of studying SCPB in ACSS is an RCT comparing unilateral SCPB with no block in patients undergoing single or two-level ACDF [20]. The primary outcome was the QoR-40 score measured at 24 h post-surgery. The patients were blinded, but the surgeon and anaesthetist were not. It was a single-centre study that enrolled 23 patients to each group. The QoR-40 scores were significantly better in the SCPB group (179 [116-195] vs. 157 [97-196]) (median [interquartile range]).

The disadvantages of this trial include the small number of patients, the lack of investigator blinding and the lack of a placebo. The chosen MCID of 10 points for the QoR-40 score is not reflective of the current literature (see above). In addition, we believe a bilateral SCBP yields superior outcomes to a unilateral block as the surgical incision can sometimes reach, or cross, the midline. Finally, the block was landmark-based, rather than ultrasound-guided. Ultrasound-guided SCPB has greater efficacy and reduced local anaesthetic toxicity compared to the landmark technique [24, 25]. The design of our proposed trial addresses each of these issues.

Placebo-controlled trials are particularly important when outcomes are based on patients’ subjective rating [26]. This trial is justified because there is a need to [1] demonstrate the true treatment effect of this intervention, [2] control for the bias that is associated with the tangible intervention and [3] provide a quantification of the adverse events of this intervention.

The anticipated benefits of SCPB in ACSS include improved post-operative pain control, resulting in a reduced length of hospital stay, decreased opioid requirements and an improved patient experience. Alternatively, this placebo-controlled trial may demonstrate no benefit from SCPB, and in that case, an unnecessary percutaneous procedure and administration of a medication will be avoided.

Potential limitations of this trial include a possible slow rate of recruitment secondary to patient concern over participating in an interventional placebo trial. This is a well-known issue for placebo trials (in surgery in particular); however, these trials are important and have been shown to be feasible [27, 28]. Second, we have chosen a power of 80% in our sample size calculation. Whilst this could be regarded as low power, it is consistent with conventional values; although we do acknowledge the possibility of type II error if the effect size is not as strong as predicted [29].

### Trial status

The trial is in the recruitment stage. The first patient was enrolled on October 21, 2019. Seventeen patients have been recruited to date. This is protocol version 11 (11/6/21). Recruitment is anticipated to be completed in October 2022.

## Data Availability

Not applicable.

## Abbreviations

ACDF: Anterior cervical discectomy and fusion
ACSS: Anterior cervical spine surgery
GA: General anaesthesia
HDU: High dependency unit
HREC: Human Research Ethics Committee
MCID: Minimum clinically important difference
PONV: Post-operative nausea and vomiting
RCT: Randomised controlled trial
SCPB: Superficial cervical plexus block
QoR-40: 40-item quality of recovery
